## Materials and methods

### Study design

The study is a prospective, randomized, double-blind controlled clinical trial to compare different induction therapeutic strategies in kidney transplant recipients. This study will enroll 70 subjects in each arm. Figure 1 presents a high-level overview of the study procedures. A schedule of assessments is provided in Appendix.

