### Randomization and blinding

After fulfilling the enrolment criteria and obtaining the informed consent, subjects will be randomized to receive either the standard therapy (Arm I) or placebo (no induction) (Arm II) with a 1:1 allocation, as specified in the intervention section below. A randomization algorithm has been generated by the statistician. The randomization algorithm will be maintained by the Department of Pharmacy and has been generated via the ralloc procedure in Stata™ (Jones and Kenward version 3.7.6), with block randomization: subjects will be divided into subgroups called blocks (block size: 8), such that the variability within blocks is less than the variability between blocks. Then, subjects within each block are randomly assigned to either group. The algorithm will be used to randomize patient following signing the informed consent and admission.

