### Statistical methods

The sample size projection is based upon historical data from transplants in 2018 and for which at least 1 year of follow-up has been achieved. These number 16 subjects and from whom one suffered rejection within the year, i.e., a rate of 0.0625. A margin of non-inferiority is proposed such that the true rejection rate among those treated without Simulect® would not be more than 15%, i.e., a margin of 0.0875 (0.1500 minus 0.0625). We recruit patients for the study and calculate a 95% confidence interval for the true rejection rate among those treated without Simulect®. This confidence interval will be P ± SE(p). We wish that the confidence interval for the rate to be at least 0.0875. The standard error of p is SQRT(p(1-p)/n). Solving for *n* yields a value of approximately 64. Accounting for loss to follow-up and other logistical issues, we have added to this number. We propose that the sample size in each arm be 70 subjects.

Statistical analysis will be performed using SAS/JMP Version 14 (SAS Institute, Cary, NC). Baseline parametric data will be expressed as means of and standard deviations and any differences in the groups will be analyzed with the paired Student’s *t* test, the chi-square test, or the Mann-Whitney *U* test as appropriate. *P* values less than 0.05 will be considered statistically significant. Multivariate analysis will be used to adjust for other risk factors including the concomitant administration of other interacting medications such immunosuppressants. Kaplan-Meier survival analyses will be used to compare outcomes for patient survival, graft survival, rejection, and BK nephropathy. Univariate and multivariable stepwise. Cox regression analyses will be performed to determine risk factors associated with patient death, graft loss, and rejection. We will also use propensity score analyses as an additional means to account for group differences in baseline characteristics. A propensity score represents the likelihood of a patient receiving a particular treatment or, in this case, no basiliximab induction instead of two doses of basiliximab. Data analysis will be carried out after completion of therapy in retrospective manner.

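### The paired Student's t test is named for comparing two independently randomised arms that contain no pairs

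*Protocol article*

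**What the plan says.** The Statistical methods section opens its analysis paragraph with baseline data: "Baseline parametric data will be expressed as means of and standard deviations". The same sentence then says that "any differences in the groups will be analyzed with the paired" Student's t test, and lists chi-square and Mann-Whitney U as alternatives, with the choice left to what suits the data.

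The design is a parallel comparison. Randomization and blinding states that "subjects will be randomized to receive either the standard therapy (Arm I) or placebo (no induction) (Arm II) with a 1:1 allocation". It describes blocks of size 8 and adds that "subjects within each block are randomly assigned to either group". Study design states: "This study will enroll 70 subjects in each arm". No section describes matching, crossover or any other link between a patient in one arm and a patient in the other.

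For rejection, Statistical methods names other tools: a 95% confidence interval for the rate without basiliximab, Kaplan-Meier analysis and Cox regression.

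**The concern.** A paired t test works on within-pair differences, so it needs a defined partner for each observation. Two independently randomised arms supply none. Anyone who runs the test as named must invent the pairs, usually by file order. The result is then neither reproducible from the data alone nor able to use every patient when the arms are unequal.

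The scope is wider than one baseline table. The sentence begins with baseline data but goes on to cover any group differences, and no other two-sample test for continuous data is named. The protocol has continuous secondary measures: eGFR at 6 and 12 months (Abstract), and calculated GFR and CD25 receptor numbers (Study end points). An analyst could reasonably carry the same test to these.

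**Working it through.** The plan gives no figure for this comparison, so there is none to reproduce.

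**Inputs.** 70 patients per arm, 1:1 allocation and block size 8 (Study design; Randomization and blinding); significance at P < 0.05 and an increase from about 64 to 70 per arm for loss to follow-up and logistics (Statistical methods).

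**1. Do the blocks create pairs?** No. A block of 8 at 1:1 holds 4 patients per arm in random order. It balances numbers over time and does not tie any one patient to another.

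**2. Will the arms be equal?** This cannot be relied on. If one list is stopped at 140 patients (an assumption), 140 / 8 = 17.5. The 17 full blocks give 17 × 4 = 68 per arm, and the last 4 patients need not split 2:2, so an arm could end anywhere from 68 to 72. The loss to follow-up that the protocol expects can add further imbalance. A paired test then discards the surplus patients in the larger arm.

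**3. How far does the P value depend on row order?** With equal standard deviations s in the two arms, the within-pair differences have variance 2s²(1 − r), where r is the correlation produced by the chosen pairing. Hence

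t(paired) = t(independent) / √(1 − r).

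Under arbitrary pairing, r averages 0 with a standard deviation of about 1/√(70 − 1) = 0.120. Take a difference exactly at two-sided P = 0.05 in the independent test, t = 1.977 on 70 + 70 − 2 = 138 degrees of freedom. At two standard deviations of r either way, on 70 − 1 = 69 degrees of freedom:

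- r = +0.24: t = 1.977 / √0.76 = 2.268, P = 0.026
- r = −0.24: t = 1.977 / √1.24 = 1.776, P = 0.080

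Re-pairing one simulated data set of this kind 20,000 times agreed: 95% of the P values lay between 0.027 and 0.079, and 45% were below 0.05. The same patients and measurements give either conclusion.

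**4. What does not change.** The t critical value rises only from 1.977 (138 df) to 1.995 (69 df). The long-run type I error also stays near 5%: simulations of 50,000 trials with 70 arbitrary pairs gave 4.9% and 5.1%. The sample size involves no t test: the stated 64 is reproduced by a single-proportion formula, 1.96² × 0.15 × 0.85 / 0.0875² = 64.0.

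**The case against.** **The list is qualified and concerns baseline data.** The sentence leaves the choice to whatever suits the data, and its stated subject is baseline. That limits the importance of the error but does not cure it. The qualifier chooses among three listed tests, and for normally distributed data the only one listed is paired. Mann-Whitney U, the counterpart for non-normal data, is an independent-samples test, so the same two arms would be treated as paired or independent according to the shape of the distribution.

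**A paired test has a proper use in this trial.** One secondary outcome compares calculated with measured GFR, which is a within-patient comparison. The sentence, however, assigns the test to differences between groups.

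**The practical harm is modest.** This stands. The error rate over repeated trials is about right and the loss of degrees of freedom is trivial. What is lost is a single reproducible answer, and patients when the arms are unequal.

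A reader might infer stronger points that the document does not support:

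- *That chi-square is invalid for rejection because few events are expected.* The text does not assign chi-square to rejection. At the historical rate ("These number 16 subjects and from whom one suffered rejection within the year, i.e., a rate of 0.0625"), 70 × 0.0625 = 4.4 events are expected per arm. If the no-induction arm were at 15% it would expect 70 × 0.15 = 10.5, a mean of 7.4 per arm. Exact enumeration at 70 per arm with 6.25% in both gives a type I error of 5.01% for the uncorrected chi-square test and 1.74% for Fisher's test. At 6.25% against 15%, power is 39.6% and 29.7%. Chi-square holds its level, and changing to Fisher would cost power.
- *That all the named tests are wrong.* Mann-Whitney U fits two independent arms, and chi-square fits categorical data.
- *That significant baseline differences will drive the covariate adjustment and propensity score.* The text lists those analyses without making them depend on baseline P values. Testing baseline differences after randomisation is uninformative, but it is a matter of reporting and contradicts nothing here.

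**Conclusion.** The paired t test is wrong as written for any comparison between the arms. The conclusion rests only on the stated design: individual randomisation to parallel arms without matching. The size given, P from about 0.03 to 0.08 across pairings, is for a borderline difference with 70 complete patients per arm and equal standard deviations. Differences far from the 0.05 threshold would seldom change sides.

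The reach is the comparison of normally distributed continuous data: baseline variables for certain, and continuous secondary outcomes such as GFR on a reasonable reading of the sentence. The binary primary endpoint, its named analyses and the sample size are unaffected. This is a clear error of limited consequence, worth correcting before analysis.

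**What to change.** In Statistical methods, replace the paired Student's t test with an independent two-sample (Welch) t test. Leave the chi-square and Mann-Whitney U tests as listed. If a paired test was meant for the within-patient comparison of calculated with measured GFR, say so in a separate sentence tied to that outcome. Any separate statistical analysis plan should carry the same wording.

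The cost is one phrase. Enrolment, data collection and trial conduct do not change.

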## Introduction

The standard immunosuppression protocols for solid organ transplantation have evolved to permit reliable short-term graft survival, such that transplantation has become the preferred therapy for end-stage organ failure. In the case of renal transplantation, graft and patient survival exceed 90% during the first post-transplant year [1–3].

Two antibodies have been constructed and produced by recombinant DNA techniques from mouse myeloma cell lines: basiliximab, a chimeric monoclonal antibody which includes the entire murine variable region and is approximately 80% human, and daclizumab, a humanized monoclonal antibody which includes only the hypervariable murine component and is approximately 90% human [4–10]. Only basiliximab is currently on the market with the trade name of Simulect® (basiliximab, Novartis) while Zenapax® (daclizumab, Roche) was withdrawn from the market and have shown virtually the same results in phase III clinical trials, although a randomized, prospective, well-powered study between the two drugs using the currently recommended dosage schedules has not been performed [6, 9, 11–13].

Importantly, the phase II data established that serum basiliximab concentrations exceeding 0.2 μg/ml were sufficient to saturate CD25 on circulating T lymphocytes in vivo [14–16]. Interestingly, the phase II studies were carried out to determine the antibody dose during the first 4 to 6 weeks post-transplant which could achieve this concentration. This concentration can be achieved with single dose basiliximab, i.e., 20 mg [16, 17]. Clinical trials leading to the US FDA drug approval were mainly coupled with cyclosporin as main maintenance immunosuppressant drug. However, the use of basiliximab induction when combined with tacrolimus-based immunosuppression has not been thoroughly investigated in well-structured, randomized clinical trials [18].

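### Stepwise Cox models for risk factors are planned on about 9 expected rejections, which gives low power, exaggerated hazard ratios and a material chance of spurious selections

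*Protocol article*

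**What the plan says.** The protocol article, under Statistical methods, contains the fragment "Univariate and multivariable stepwise", closed by a full stop, and then the sentence "Cox regression analyses will be performed to determine risk factors associated with patient death, graft loss, and rejection". The stop looks like a slip of typing, and the two pieces read naturally as one method applied to three outcomes. The same section sets 0.05 as the significance threshold. It also foresees multivariate adjustment for further risk factors, interacting medications among them, without a list or a limit. It does not call the risk-factor models exploratory.

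The figures that determine the number of events are in the same document:

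- Rejection rate: "These number 16 subjects and from whom one suffered rejection within the year, i.e., a rate of 0.0625" (Statistical methods).
- Size: "We propose that the sample size in each arm be 70 subjects" (Statistical methods) and "This study will enroll 70 subjects in each arm" (Study design), "with a 1:1 allocation" (Randomization and blinding).
- Death and graft loss: no planning figure. The Introduction says only that in renal transplantation generally "graft and patient survival exceed 90% during the first post-transplant year".

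Statistical methods separately plans Kaplan-Meier comparisons of patient survival, graft survival and rejection.

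**The concern.** Univariate screening followed by stepwise selection needs many events per candidate variable to give results that can be trusted. The protocol never sets the number of events it expects beside the models it plans. If that number is around 9, three things follow. Real factors of moderate size are mostly missed. Any factor that is selected carries a hazard ratio well above its true value. The P values and intervals after selection are those of a model treated as if it had been fixed in advance, so they overstate the evidence.

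At stake is a published list of risk factors for rejection, death or graft loss that a reader could take at face value, beside a primary result that also rests on few events.

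**Working it through.** **1. The plan's own figure.** The protocol states a sample size but no expected event count. Its size follows from n = z²·p(1−p)/w² with w = 0.0875. With p = 0.15 and z = 1.96, n = 3.8415 × 0.1275 / 0.00765625 = 63.97, which agrees with "yields a value of approximately 64". The step from 64 to 70 per arm is an allowance of 1 − 64/70 = 8.6%.

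**2. Expected rejections.**

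| Scenario | 70 per arm | 64 per arm |
|---|---|---|
| 0.0625 in both arms | 140 × 0.0625 = 8.75 | 128 × 0.0625 = 8.0 |
| 0.0625 with basiliximab, 0.15 without | 70 × 0.2125 = 14.9 | 64 × 0.2125 = 13.6 |

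Under Binomial(140, 0.0625) the central 95% range is 4 to 15 events, and the probability of 20 or more is about 0.0005. That range takes the rate as known. The exact 95% interval for 1 of 16 runs from 0.2% to 30%, so the true expectation is far less certain than 8.75 suggests.

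**3. Deaths and graft losses.** Survival above 90% bounds each below 14 of 140. Assumed one-year rates of 1%, 2% and 5% give 1.4, 2.8 and 7 events.

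**4. Power for a real factor.** For a balanced binary factor, two-sided 0.05, Schoenfeld's approximation is power = Φ(√(d/4)·ln HR − 1.96), with d events.

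- d = 9, HR 2: 1.5 × 0.693 − 1.96 = −0.920, power 18%.
- d = 9, HR 3: 1.5 × 1.099 − 1.96 = −0.312, power 38%.
- d = 15: 27% for HR 2 and 57% for HR 3.
- For 80% power, HR = exp(2.80/√(d/4)), which is about 6.5 at 9 events and 4.2 at 15.

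**5. Exaggeration.** On the same approximation, a factor reaches P<0.05 only if its observed hazard ratio is at least exp(1.96/√(d/4)). At 9 events that is exp(1.307) = 3.7; at 15 events it is exp(1.012) = 2.8. A real factor with a hazard ratio of 2 can therefore be selected only when its estimate is inflated.

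**6. Spurious selection.** Forward stepwise Cox regression was simulated with 140 patients, one year of follow-up, entry at P<0.05 and noise covariates only (alternately normal and binary). The first step of forward selection acts as a univariate screen. The number of candidates is assumed.

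| Candidates | Mean events | Runs | At least one noise factor selected | Median largest HR when any selected |
|---|---|---|---|---|
| 5 | 8.6 | 300 | 27% | 4.4 |
| 10 | 8.8 | 300 | 43% | 4.4 |
| 10 | 15.0 | 200 | 42% | 3.0 |

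The Monte Carlo standard error is about 3 percentage points. The independence approximation 1 − 0.95^k gives 23% for k = 5 and 40% for k = 10. The spurious-selection rate thus depends on how many candidates are screened and hardly on the event count. The event count drives the low power and the inflated hazard ratios.

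**The case against.** The strongest reply is that these are secondary models, that the analysis plan is not shown and may name and limit the covariates, and that the event count is a guess from 16 patients.

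The first part stands: the non-inferiority criterion is built on a confidence interval for the rejection rate, not on these models. The second part stands only for the covariate list, because stepwise selection is already fixed in the protocol text. The third part is right about the uncertainty, but the more favourable planning scenario of about 15 events leaves the conclusion unchanged.

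Four stronger readings are tempting, and the documents do not support them:

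- **The models will select noise, or their findings will be mostly chance.** In the simulation, 57% to 73% of runs selected nothing spurious. A simulation without real factors cannot say what share of reported factors would be false.
- **Treatment may drop out of the model on its P value.** The stated aim of the Cox models is to find risk factors. The text does not say whether treatment enters the stepwise pool or is forced in, nor that a treatment hazard ratio will be taken from the selected model.
- **Deaths and graft losses will be rarer than rejections.** The only figure is a general background statement whose bound (below 14 of 140) lies above 8.75. Study end points also lists survival beyond one year, so these events need not stop at 12 months.
- **The primary conclusion is compromised.** Nothing in the plan links it to these models.

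**Conclusion.** The concern holds as a point about secondary analyses. The protocol fixes a data-driven selection method for which its own planning figures give about 9 rejections, or about 15 at the 15% limit. At 9 events, power is about 18% for a hazard ratio of 2, and an observed hazard ratio must reach about 3.7 to be selected. The chance of at least one spurious factor is roughly 27% to 43%, and the P values take no account of the selection.

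This rests on three assumptions: a rate of 6.25% that comes from 1 of 16 patients, a balanced binary factor for the power figures, and 5 to 10 candidates screened at P<0.05. It is worth correcting before the data are analysed, but it is no obstacle to the trial.

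**What to change.** Delete univariate screening and stepwise selection from Statistical methods. For time to first rejection, specify one Cox model, preferably Firth-penalised, with treatment forced in and at most one baseline covariate named in advance (HLA mismatch count is one candidate), and label it exploratory. Two parameters on 8.75 events is 4.4 events each, which is why penalisation and the label are advisable. Report deaths and graft losses as counts with Kaplan-Meier estimates and confidence intervals by arm, and model them only if the events turn out to be sufficient by a threshold written down beforehand. Penalisation and the choice of covariate are matters of judgement; the essential elements are a prespecified model, a cap on its size and the exploratory label.

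The cost is a change of wording in the protocol, mirrored in the analysis plan, with no extra patients or data. What is lost is an exploratory list of risk factors.

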## Treatment (interventions)

*Arm 1*: Two doses of basiliximab, 20 mg intravenously, at 0 and 4 days post engraftment. The first dose to be given prior to reperfusion*Arm 2*: No induction (i.e., 100 ml of normal saline) will be administered intravenously, at 0 and 4 days post engraftment.

### Labeling, handling, and storage

Packaging and labeling of basiliximab and placebo will be performed under responsibility of study pharmacist in accordance with GMP/GCP and national regulatory requirements. All study products will be stored, inventoried, reconciled, and destroyed according to applicable regulations. The product will be labeled according to SFDA regulations as follows:

The specific order sentence with (i.e., BASILIXIMAB RAC#2191 177) will be used to the purpose of prescribing the drug for those who have consented to participate in the study.

Medications are properly and safely stored as per King Faisal Specialist Hospital & Research Centre regulations and policies. Medications are stored under necessary conditions: vials refrigerated at 2 to 8 °C (36 to 46 °F).

### Medication dosage and administration

A protocol was developed for immunosuppressive for renal transplant recipients. This protocol represents the overall knowledge, experience, and wisdom of the renal transplant team members according to the best available evidence but is not meant to substitute the general clinical judgment of transplant practitioners. All transplant team members are expected to follow this protocol and deviation from it is only allowed when clinically justified and after consultation with other team members. The 2016 September revision will be followed (Additional file 1).

The placebo is the solution for injection [i.e., 100 ml of normal saline] without basiliximab that is going to be prepared by the research team pharmacist.

### Concomitant medications

Primary immunosuppressive therapy with tacrolimus, anti-proliferative mycophenolate or azathioprine, and steroids. Those medications shall be started 3 days prior to the scheduled day of transplant. Other agents are prohibited.

## Study end points

A.Primary outcomes
Biopsy-proven acute rejection within first year after transplantB.Secondary outcomes
One-year patient and graft survivalEmergence of de novo donor-specific antibodies (DSAs)Composite of measured glomerular filtration rate (GFR) < 60 mL/min/1.73 m^2^ at month 6 and/or 12A decrease in measured GFR ≥ 10 mL/min/1.73 m^2^ from month 3 to month 12Time to first acute rejectionType and severity of rejection, requirement of antilymphocyte antibody therapy, or steroid-resistant rejectionClinically treated acute rejection episodesNumber of acute rejection episodesAny infection (CMV, BKV, urinary tract infection, etc.)Patient and graft survival beyond 1 yearTo assess the difference in calculated and measured GFRCalculated glomerular filtration rate by Cockcroft-Gault equationTo determine the absolute and relative number of CD25 receptors on T cells at the end of each dosing intervalNew onset diabetes after transplantSlow/delayed graft function (delayed graft function will be defined as the need for dialysis within the first week after transplantation. Slow graft function was defined as a serum creatinine level exceeding 3.0 mg per deciliter on day 5 that did not require treatment with dialysis) [19]

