**Expected outcomes:**

1. Primary outcomes:

Biopsy-proven acute rejection within first year following transplant

2. Secondary outcomes:

a. Patient and graft survival at 1 year

b. eGFR at 6 months and at 12 months

c. Emergence of de novo donor-specific antibodies (DSAs)

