## Efficacy assessments

Serum creatinine will be monitored and collected at the following time intervals: at baseline and at weeks 2, 4, 12, 24, 36, and 48. Liver function tests, complete blood count and hematology, chemistry, and other laboratory tests will be collectedBiopsy will be carried out based on the discretion of the primary treating consultant (see Appendix). All biopsy will be interpreted according to Banff classification [20] by independent pathologist

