**Acute rejection**	*Acute rejection* will be defined as a clinico-pathological event requiring clinical evidence and biopsy confirmation. Allograft biopsies will be evaluated for the presence and severity of acute rejection by a blinded central independent pathologist using Banff 97 working classification of kidney transplant pathology. In the analyses of acute rejection, the biopsy interpretation and grading by the central pathologist will supersede local interpretation. Biopsies performed for suspected acute rejection that do not fully meet the criteria but are interpreted by the central pathologist as acute rejection and result in treatment for acute rejection, will be counted as acute rejection. *Subclinical rejection* is defined as histological findings by the central pathologist consistent with acute rejection, but lacking its clinical correlate. *Steroid-resistant acute rejection* is defined as the use of lymphocyte-depletion therapy following treatment with corticosteroids.		
**Bone profile**	Serum calcium, albumin, phosphorus, and magnesium		
**Chemistry**	Glucose, potassium, sodium, chloride		
**Chronic allograft nephropathy (CAN)**	Biopsy-proven CAN will be determined by a central histopathologist using the Banff working classification of kidney transplant pathology.		
**Coagulation**	INR, prothrombin time (PT), activated partial thromboplastin time (APTT)		
**Creatinine clearance**	Creatinine clearance is calculated by the Cockcroft-Gault equation using ideal body weight (IBW). Male: CLcr (mL/min) = [140 − age (years)] × BW (kg)/72 × Scr Female: CLcr (mL/min) = [140 − age (years)] × BW (kg) × 0.85/72 × Scr		
**Criteria for performing an allograft biopsy to assess for acute rejection**	1. An unexplained rise of serum creatinine ≥25% from baseline creatinine 2. An unexplained decreased urine output 3. A serum creatinine that remains elevated within 14 days post-transplantation and clinical suspicion of acute rejection exists		
**delayed graft function (DGF)**	A subject will be determined to have DGF if the subject is treated with dialysis within the first week (days 1–7) post transplantation.		
**Graft Loss**	Graft loss is defined as either functional loss or physical loss. Functional loss will be defined as a sustained level of SCr ≥ 6.0 mg/dL (530 μmol/L) as determined by the central laboratory for ≥4 weeks or ≥ 56 consecutive days of dialysis, or impairment of renal function to such a degree that the subject undergoes re-transplant		

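### The abstract promises eGFR at 6 and 12 months, but the endpoint section substitutes two cut-point outcomes on measured GFR, for which no method or visit is described

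*Protocol article*

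**What the plan says.** Four places in the protocol article bear on renal function.

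- **Abstract, expected outcomes.** The renal secondary outcome is "eGFR at 6 months and at 12 months": an estimated value at two times, with no threshold.
- **Study end points, secondary outcomes.** The first renal item is "Composite of measured glomerular filtration rate (GFR) < 60" mL/min/1.73 m² at month 6 and/or month 12. The next is a fall in measured GFR of 10 mL/min/1.73 m² or more between months 3 and 12. Further down come a comparison of calculated with measured GFR, and calculated GFR by Cockcroft-Gault with neither threshold nor time point. Slow or delayed graft function is also listed ("delayed graft function will be defined as the need for dialysis within the first week after transplantation").
- **Efficacy assessments and the Schedule of Assessment.** The renal measurement named is creatinine: "Serum creatinine will be monitored and collected at the following time intervals: at baseline and at weeks 2, 4, 12, 24, 36, and 48". Other laboratory tests are mentioned generically, and the schedule has a single laboratory row covering every visit.
- **Definitions (Table 2).** The only clearance method given is "Creatinine clearance is calculated by the Cockcroft-Gault equation using ideal body weight (IBW"), with results in mL/min.

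The randomised treatment is given "at 0 and 4 days post engraftment" (Treatment section).

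**The concern.** Estimated and measured GFR are different quantities, and a value at a visit is a different outcome from a yes/no cut. The abstract and the endpoint section therefore do not specify the same renal comparison. A reader cannot tell which one the trial will report, and the choice could be made after the data are seen.

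Three listed items need measured GFR: the below-60 composite, the decline, and the calculated-versus-measured comparison. The article describes no procedure that would produce it.

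The decline outcome takes as its starting point a value that treatment may already have affected. The trial asks whether induction can be omitted without harm, so an outcome that cannot see early loss is a weak renal comparison. Cutting GFR at 60 also discards information in a trial of 70 per arm.

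**Working it through.** **1. The wording side by side**

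| Feature | Abstract | Study end points |
|---|---|---|
| Quantity | Estimated GFR | Measured GFR (three items); Cockcroft-Gault (one item) |
| Form | Value | Below 60; fall of 10 or more; Cockcroft-Gault uncut |
| Time | 6 and 12 months | Month 6 and/or 12; month 3 to 12; none given for Cockcroft-Gault |
| Indexed to 1.73 m² | Not stated | Yes for the thresholds; no for Cockcroft-Gault (mL/min) |

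The term measured is not a slip for estimated, because the same list compares calculated with measured GFR. The Cockcroft-Gault item does not restore the abstract's outcome as written, since it has no time point.

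**2. The plan's own figures**

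No mean, SD, effect size or power is stated for any renal outcome, so there is no renal figure to reproduce. The sample size concerns rejection. With p = 0.15 and half-width 0.15 − 0.0625 = 0.0875, n = 1.96² × 0.15 × 0.85 / 0.0875² = 63.97, which matches the stated 64 before the increase to 70 per arm. I use 64 per arm below as the evaluable number.

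**3. Cost of the cut at 60 (illustration)**

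Assumptions, none from the documents: normally distributed GFR, true difference 8 mL/min/1.73 m², SD 15 or 20, better-arm mean 55 to 70, two-sided 5%, one visit.

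Continuous value: power = Φ(8 / (SD × √(2/64)) − 1.96).
- SD 15: Φ(8/2.652 − 1.96) = Φ(1.06) = 86% (0.855).
- SD 20: Φ(8/3.536 − 1.96) = Φ(0.30) = 62%.

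Cut at 60: with better-arm mean m, p₁ = Φ((60 − m)/SD) and p₂ = Φ((60 − m + 8)/SD). These enter a normal-approximation test of two proportions. Each range below gives the lowest and highest result over both the pooled and the unpooled variance under the null.

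| SD | Better-arm mean | Share below 60, by arm | Power, cut | Power, continuous |
|---|---|---|---|---|
| 15 | 55 | 63.1% v 80.7% | 60–62% | 86% |
| 15 | 65 | 36.9% v 57.9% | 67–68% | 86% |
| 20 | 55 | 59.9% v 74.2% | 41–42% | 62% |
| 20 | 65 | 40.1% v 56.0% | 43–44% | 62% |

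Means of 60 and 70 fall within these ranges. The loss is roughly 17 to 25 percentage points. For 80% power, the continuous value needs 56 per arm at SD 15 and 99 at SD 20. The cut outcome needs 88–101 and 156–168, about 1.6 to 1.8 times as many.

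**4. The month-3 starting point**

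Dosing is on days 0 and 4, so month 3 follows both randomisation and treatment. Suppose one arm loses GFR only before month 3, and both arms then have mean change 0. The chance of a fall of 10 or more is Φ(−10/SD of change). For assumed SDs of change of 8, 10 and 12 it is 10.6%, 15.9% and 20.2%, the same in both arms. The expected arm difference is 0, however large the early loss was.

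**The case against.** **Measured GFR may be collected.** The laboratory entries are generic, and the case report form and institutional protocol are additional files not shown. The schedule is plainly condensed, since it has no row for CD25 counts or for the day-5 and week-8 tacrolimus troughs. This stands. A reader might infer that measured GFR is never collected and that these outcomes cannot be computed. The article supports only that no method or visit is described.

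**Not every renal outcome is measured or cut.** This also stands. Calculated GFR is listed uncut and could be computed from the week 24 and 48 creatinine. Nothing in the text applies Cockcroft-Gault to the thresholds of 60 or 10. The missing index matters only if the calculated value is meant to stand in for them.

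**The month-3 reference is legitimate.** The first dose precedes reperfusion, so no pre-treatment graft GFR exists, and later decline is a fair question. Early injury can still show in slow or delayed graft function, in rejection, and in the month 6/12 level. This narrows the point to one outcome. A reader might also infer that the decline outcome could favour the arm with more early injury. The calculation shows insensitivity, not reversal, and nothing in the documents supports the stronger reading.

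**The power figures do not model the stated endpoint.** Correct: the plan's composite spans two visits, and the figures use one. They illustrate the cost of a cut and are not the power of the planned outcome.

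**Analysis detail belongs in a statistical analysis plan.** That covers the choice of model. It does not cover a contradiction between abstract and endpoint section about which quantity is compared.

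**Conclusion.** The point holds in limited form. The contradiction can be read directly from the article: eGFR values at 6 and 12 months in the abstract, against dichotomised measured GFR in the endpoint section. The article describes no way of obtaining the measured value, and the listed calculated GFR has no time point and no indexing. The month 3–12 decline cannot register loss completed before month 3. That is a limit of this one outcome, and early damage is not hidden across the trial.

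The size of the dichotomising cost, about 62–86% power falling to 41–68%, rests wholly on assumed values (8 units, SD 15–20, 64 evaluable per arm, one visit). These are secondary outcomes, so the primary rejection analysis and the sample size are unaffected.

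**What to change.** - Make the renal arm comparison creatinine-based eGFR at months 6 and 12, using one named equation indexed to 1.73 m². Analyse it as a continuous variable by randomised arm, with a stated value for graft loss, and use the same wording in abstract and body.
- Keep the share below 60 and the month 3–12 decline as descriptive, the latter labelled as later decline only.
- Either state the method and visits for measured GFR, or remove the term together with the calculated-versus-measured comparison, which would otherwise have nothing to compare.

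The eGFR route needs no new measurement, because creatinine is already collected at weeks 24 and 48. The cost is that the threshold outcomes become descriptive and the registered secondary outcomes may need updating. Keeping measured GFR means specifying its procedure and, if it is not already collected, adding it.
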